### 2.6 Outcomes and participant timeline

The study has a longitudinal design conducted over 12 months with three assessment points. Outcome measures will be collected at baseline (T1) (prior to randomisation); post-treatment (T2) (14 weeks from baseline assessment); and 12-month follow-up (T3) (12 months from start of therapy) by blinded assessors. The primary and secondary outcome measures are presented in Table 1. Measures include self-reported measures and measures administered by an independent assessor (independent clinician) blind to treatment allocation at each of the time points. In addition to blinding of treatment type by the research assistant, at the start of each assessment participants will be asked not to confer the details of their treatment, including treatment condition, to the independent assessors. Clinician-report measures (treating clinician) are also administered.

**Table 1 pone.0269981.t001:** Primary and secondary outcome measures by time interval.

Instrument	Domain	Type^a^	Time Interval^b^^a2^			Reference
			T_1_	T_2_	T_3_	
Demographic Inventory	Demographics	SR	✓	✓	✓	
GAI-20	Anxiety	SR	✓	✓	✓	[28]
GDS-30	Depression	SR	✓	✓	✓	[29]
DSI-S	Depression/Suicide	SR	✓	✓	✓	[30]
ADIS-5	Psychopathology	BA	✓	✓	✓	[24]
DJGLS-11	Social Connection	SR	✓	✓	✓	[31]
LSNS	Social Network	SR	✓	✓	✓	[32]
ACPQ-12	Social Participation	SR	✓	✓	✓	[33]
PID-5 -BF	Personality Traits	SR	✓	✓	✓	[34]
HAq-II	Therapeutic Alliance	SR		✓		[27]
AQoL	Health Related Quality of Life	SR	✓	✓	✓	[35]
Use of Care Services Questionnaire	Cost-Effectiveness	SR	✓	✓	✓	N/A
iPCQ	Cost-Effectiveness	SR	✓	✓	✓	[36]

NOTE: GAI-20 = Geriatric Anxiety Inventory– 20 items; GDS-30 = Geriatric Depression Scale– 30 items; DSI-S = Depressive Symptoms Inventory–Suicide Subscale; ADIS-5 = The Anxiety Disorders Interview Schedule 5^th^ edition; DJGLS-11 = De Jong Gierveld Loneliness Scales—11 items; Lubben Social Network Scale; ACPQ-12 = Australian Community Participation Questionnaire– 12 item; PID-5 –BF = The Personality Inventory for DSM– 5; HAq-II = Helping Alliance Questionnaire; AQoL = Assessment of Quality of Life; iPCQ = iMTA Productivity Cost Questionnaire.

^a^SR = Self-eeport scales administered by participants; OS = Observer scale administered by treating clinician; BA = Scale administered by independent blind assessor

^b^T_1_ = Baseline assessment; T_2_ = 14-week post-treatment assessment; T_3_ = 12-month follow-up assessment.

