1) Mean changes in CSR across all anxiety and depressive disorders based on the ADIS-5 at 12-month follow-up.2) Changes in symptomatology at post-treatment and 12-month follow-up on the following measures:**Geriatric Anxiety Inventory** [GAI; 28]. The GAI is a 20-item self-report measure of anxiety in older adults.**Geriatric Depression Scale** [GDS; 29]. The GDS is a 30-item self-report measure of depression for use in older adult populations.**Depressive Symptoms Inventory–Suicide Subscale** [30] is a 4-item measure of suicidal ideation.2) Changes in social participation/connection at post-treatment and 12-month follow-up on the following measures:**De Jong Gierveld Loneliness Scales** [31], which measures feelings of loneliness andperceived social isolation with 11 items.**Lubben Social Network Scale** [LSNS; 32]. The LSNS is a commonly used tool to assess social connections in older adult populations. The 18-item scale assesses the frequency and quality of family, friendship and neighbour support.**The Australian Community Participation Questionnaire-Short Form [33]** The 12-item short form of the ACPQ measures frequency of participation in seven different social activities (contact with extended family, friends and neighbours, contact with friends and family, attending organised community events, volunteering and political protest).3) Cost utility of the interventions on the following measures:**Assessment of Quality of Life** [AQoL-8D; 35, 37]. The AQoL-8D measures quality of life and health outcomes across eight domains (independent living, relationships, mental health, coping, pain, senses, self-worth, and happiness).**Use of Care Services.** The Use of Service survey is developed by the research team to assess use of health and community care services in the preceding six months, including hospital services, medical services, allied health services, community-based services, and diagnostic services, supplemented with linked data from the NSW Centre for Health Record Linkage (CHeReL) on Admitted Patient data, Emergency Department data, and Mental Health Ambulatory data, along with Medicare Benefit Schedule (MBS) and Pharmaceutical Benefit Schedule (PBS) data.**iMTA Productivity Cost Questionnaire** [iPCQ; 36]. The iPCQ is a standardised instrument to measure and value health-related productivity losses including presenteeism and absenteeism in paid and unpaid work.

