### 2.8 Recruitment

Participants will be recruited to the CEHC from general practices, primary health network, other health professional or health organisations (e.g., aged care, hospital, residential aged care). Participants can self-refer. In addition, the study will be advertised broadly to the community and general practitioners (GPs), using brochures, media and newspaper stories and advertisements, and through Beyond Blue’s professional networks. The GPs in the local area will be informed about the study and provided with a brochure about how to improve detection and screening of anxiety and depression in their older patients.

Following referral, older adults will be screened over the telephone. Intake officers will assess likely suitability for the trial based on the inclusion and exclusion criteria outlined in Section 2.4. Older adults who are likely to meet the inclusion criteria will be sent participant information and consent forms. Intake officers will follow up to review understanding of the participant information and consent forms and to answer any questions. Older adults who are interested in participating will be asked to provide written informed consent, followed by completing full baseline measures according to the study design, including the ADIS administered by clinical psychologists, psychologists, or provisional psychologists at the Macquarie University CEHC. All participants will be allocated a deidentified alpha-numeric code by the research team. If a participant is deemed eligible after completion of the baseline assessment, they will be randomly allocated to one of the two treatment conditions by the research team (see Section 2.9 Assignment of intervention), and an appointment will be scheduled for the first treatment session. The average time between randomisation and entry into therapy is estimated to be two to four weeks depending on participant flow and clinician availability. If an older adult is ineligible for enrolment in the current study, the primary reason of ineligibility will be documented. Participants who do not consent or do not meet eligibility criteria will be offered alternative services at the CEHC as appropriate and/or referred to alternative services in the local area and/or to their GP.

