### 2.11 Data management and confidentiality

To safeguard the confidentiality of the participants and to ensure proper handling of all data, processing of all data reporting complies with CONSORT recommendations and is in accordance with the National Statement on Ethical Conduct in Human Research [38]. Participants will provide electronic or written informed consent. All participant data will be allocated a deidentified code so that confidentiality is maintained during the study, and when the data are stored. Deidentified data will be stored in password protected secure online data storage repositories indefinitely at Macquarie University. Only chief investigators, the independent biostatistician, the project manager, and research assistant will have access to this deidentified data in order to facilitate assessment and welfare of participants in a crisis (telephone number, email address). This information is stored in a separate password protected file on the Macquarie University server. Linked resource utilisation data will be extracted by the NSW Centre for Health Record Linkage (CHeReL) and the Commonwealth Department of Human Services, using the personal identifiers of consenting study participants. The content data from the routine data collections will be returned to the research team in a deidentified format, so that it can be merged with trial data using the study specific IDs. This is in line with the ‘separation principle’ that ensures the maintenance of distinct and disjointed research datasets that mitigate re-identification risks.

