### 2.13 Economic evaluation

An economic evaluation will be conducted from the healthcare system perspective. Health outcomes captured through the AQoL-8D will be evaluated using Quality Adjusted Life Years (QALYs). Intervention and resulting costs per patient in the enhanced CBT group will be compared against those in the standard CBT group, and include acute care, primary care, mental health care, community care, and medication use. Data collected using the Use of Care Services survey will be supplemented with linked, individual-level Admitted Patient data, Emergency Department data and Mental Health Ambulatory data, along with Australian Government data from the Medicare Benefit Schedule (MBS) and Pharmaceutical Benefit Scheme (PBS). A cost-utility analysis will compare differences in QALYs with differences in resource use, and will be presented using an incremental cost utility ratio. This will provide a basis to make judgements on whether the enhanced CBT is cost-effective given to the price that Australian Government funders are likely willing to pay for a QALY for the target population [39]. The *iMTA Productivity Cost Questionnaire* [36] with the Australian Community Participation Questionnaire [33] will be used to estimate the value of social contributions.

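### The six-month service-use recall does not fit the visit schedule: about 12 weeks are asked about twice and about 14 to 16 weeks after T2 not at all, which matters for survey-only services and for participants without linked data

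*Protocol article*

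**What the plan says.** Section 2.6 of the Protocol article describes a survey, written by the research team, to "assess use of health and community care services in the preceding six months". Table 1 in that section ticks the "Use of Care Services Questionnaire" at T1, T2 and T3. No different recall period is given for any visit.

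Section 2.6 also fixes the timing: "Outcome measures will be collected at baseline (T1) (prior to randomisation", then "post-treatment (T2) (14 weeks from baseline assessment", then "12-month follow-up (T3) (12 months from start of therapy". Section 2.8 adds: "The average time between randomisation and entry into therapy is estimated to be two to four weeks".

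The survey is not the only cost source. Section 2.13 states: "Data collected using the Use of Care Services survey will be supplemented with linked, individual-level Admitted Patient data". It also names emergency, ambulatory mental health, MBS and PBS records, as section 2.6 does. Section 2.11 says that linkage is done "using the personal identifiers of consenting study participants". The costs compared in section 2.13 fall into five groups: acute, primary, mental health and community care, and medicines.

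**The concern.** Cost utility is part of the main aim (section 2.1), and section 2.13 sets differences in resource use against differences in QALYs. A cost per patient from baseline to T3 needs recall windows that join end to end. A fixed six-month window does so only when visits are six months apart. Here the first interval is shorter than the recall and the second is longer.

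Two things follow. Part of the T2 answer concerns use before randomisation, which treatment cannot change. And a stretch starting at T2, around the end of therapy, is never asked about. That stretch is relevant to this trial: section 3 describes patients who respond and then relapse early, and expects the enhanced programme to help maintain gains. If service use differs between arms in those weeks, the survey will not record it.

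**Working it through.** The plan gives no figure for survey coverage, so there is none to reproduce. The check is interval arithmetic, in weeks from baseline.

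**Inputs**
- Recall R = 26 (six months, section 2.6).
- T1 = 0 and T2 = 14 (section 2.6).
- T3 = L + 52, where L is the time from baseline to the start of therapy (section 2.6).
- L = 2 to 4 (section 2.8). This is an estimated average counted from randomisation. The delay from baseline to randomisation is not stated and is taken as zero; any such delay increases L. L = 0 is shown as the lower limit.

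**T2 window.** It opens at T2 − R = 14 − 26 = −12 and closes at 14. So 12 of its 26 weeks (12/26 = 46%) precede baseline. The T1 window runs from −26 to 0, so the same 12 weeks are asked about twice.

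**Gap.** The T3 window opens at T3 − R = L + 26. The time in no survey window is (L + 26) − 14 = L + 12.

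| L | T3 | T3 window opens | Gap | Gap / T3 |
|---|---|---|---|---|
| 0 | 52 | 26 | 12 | 12/52 = 23% |
| 2 | 54 | 28 | 14 | 14/54 = 26% |
| 4 | 56 | 30 | 16 | 16/56 = 29% |

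Calendar months (R = 26.09) change these figures by about 0.1 week.

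**Which costs are exposed.** Linked records extracted by date have neither overlap nor gap. On a plain reading they serve acute care, primary care, mental health care and medicines, at least in part. No linked source is named for community care, which is both a cost group in section 2.13 and a survey item in section 2.6. For a participant who does not consent to linkage, every item rests on the survey.

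**Effect on the cost difference.** Write the T2 total as pre + post. The pre part precedes randomisation, so its expected value is equal between arms, and the expected difference in totals equals the expected difference in post. Using the total whole raises the mean in both arms and adds variance, but does not shift the expected difference. The gap acts differently: any difference arising from week 14 to week 28 or 30 is absent from the survey total.

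**The case against.** The strongest reply is that the plan already names a second source without this fault, and that it reaches most of the cost groups. This stands for the services covered and the participants linked. It does not dispose of the point, because the linked data are described as a supplement to the survey, community care has no named linked source, and linkage depends on consent.

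A second reply is that the article does not say how survey answers become costs, and that such a rule may sit in a document not shown. This also stands. A reader might infer that 12 pre-baseline weeks are booked as post-baseline cost. The article does not say that T2 totals are entered whole or added to T3. The mismatch of windows is a stated design feature; the costing error is only a possible consequence of it.

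Three further readings go too far. The 26% to 29% is a share of time without survey coverage, not a share of cost missing. The overlap does not bias the incremental cost, since it is balanced in expectation. And a mismatch between the cost and QALY periods cannot be asserted: the AQoL-8D is collected at all three visits, but section 2.13 states no QALY horizon or method.

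**Conclusion.** The point holds in a limited form. One six-month recall at these three visits makes the T2 survey overlap T1 and leaves a stretch after T2 uncovered. The 12-week overlap follows directly from the stated timings. The 14-to-16-week gap rests on the two-to-four-week wait for therapy, but a gap remains at any value of L, and is never below 12 weeks.

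The uncorrected problem is confined to survey-only items (community-based services and services outside MBS and PBS) and to participants without linkage. The documents do not give the size of either, so the effect on the cost-utility ratio cannot be stated. Within that part, the gap matters more than the overlap: it can remove a real difference between arms, whereas the overlap mainly adds noise. The primary outcome and the clinical efficacy analyses are untouched.

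**What to change.** - **Remaining visits.** Word the T2 survey as 'since your baseline assessment' and the T3 survey as 'since your last assessment', with the date pre-filled. The windows then join from baseline to T3.
- **Main source.** State that dated linked records are the main cost source for every category they cover, from baseline to T3, with the survey used only where they do not reach.
- **Forms already collected.** For survey-only items, pro-rate the T2 total to the 14 post-baseline weeks (factor 14/26 = 0.54). Interpolate use across the gap from the T2 and T3 rates, with a sensitivity analysis that varies the rate in the gap.

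The change costs form wording and a short costing rule. It has three drawbacks. T3 recall lengthens to 40 to 42 weeks (54 − 14 to 56 − 14), or a little over nine months, in people aged 65 or older. Two recall wordings are mixed in one dataset, so the wording used should be recorded for each form. Pro-rating assumes even use over the 26 weeks; if the arms differ only after baseline, it also shrinks that difference to 54% of its value. The unscaled T2 total should therefore be reported beside it, because its expected difference between arms is not shifted.

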### 2.7 Sample size

Based on review of the available literature and our pilot study results comparing this enhanced CBT program to an active control group, we predict the enhanced CBT program to produce a controlled effect size (against standard intervention) of Cohen’s *d* = 0.5. Therefore, based on a moderate effect of Cohen’s *d* = 0.5, with power at 90% and, alpha at 0.05 (two-sided), 172 participants (86 equally randomised to each condition) in total are required, with the expectation that 15% of participants will be unsuitable based on outcomes of the baseline assessment (based on previous studies in our clinic that use a brief intake screener to determine likely eligibility into the program prior to baseline assessment), at least 200 participants will be recruited. In order to understand the representativeness of the population, demographic information will be collected with respect to sex, age, country of birth, ethnicity, education, marital status, income, employment status, living circumstances (e.g., retirement villages), pre-existing health conditions, psychiatric history (including duration), and current medications (type, dosage, and frequency) at time of intake/baseline assessment, post-treatment, and at each follow-up assessment.

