**Methods:**

A total of 172 community-dwelling adults aged 65 years or older with an anxiety and/or depressive disorder will be randomly allocated to either an enhanced CBT plus social participation program (n = 86) or standard CBT (n = 86). Both treatments will be delivered during 12 weekly individual sessions utilising structured manuals and workbooks. Participants will be assessed at pre-treatment, post-treatment, and 12-month follow-up. The primary outcome evaluates mean change in clinician-rated diagnostic severity of anxiety and depressive disorders from baseline to post-treatment (primary endpoint) based on a semi-structured diagnostic interview. Secondary outcomes evaluate changes in symptomatology on self-report anxiety and depression measures, as well as changes in social/community participation, social network, and perceived social support, loneliness, quality of life, and use of health services. Economic benefits will be evaluated using a cost-utility analysis to derive the incremental cost utility ratios for the enhanced CBT program.

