### 2.9 Assignment of intervention

Eligible participants will be randomly allocated to receive enhanced CBT or standard CBT in a 1:1 ratio. The randomisation schedule will be generated using a computerised randomiser (www.randomizer.org) and placed into consecutively numbered sealed envelopes by an independent statistician. Block randomisation will be used to ensure that the two comparison groups are the same size.

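### The 172 to be randomised is exactly the number that must be analysed for 90% power; the 15% allowance is used up before randomisation, so nothing is allowed for loss by T2

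*Protocol article*

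**What the plan says.** Section 2.7 predicts a standardised difference of 0.5 between enhanced and standard CBT and gives the sample size in full: "with power at 90% and, alpha at 0.05 (two-sided), 172 participants (86 equally randomised to each condition) in total are required". The Abstract uses the same figure as the number randomised: "A total of 172 community-dwelling adults aged 65 years or older with an anxiety and/or depressive disorder will be randomly allocated".

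The same sentence of section 2.7 joins the allowance to that figure: "172 participants (86 equally randomised to each condition) in total are required, with the expectation that 15% of participants will be unsuitable". It ties the unsuitability to the outcome of the baseline assessment and concludes that "at least 200 participants will be recruited". Section 2.8 fixes the order of events: only a person judged eligible once the baseline assessment is complete goes on to be randomised.

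Elsewhere the protocol foresees loss after randomisation. Section 2.10 covers participants who miss an assessment, withdraw consent or can no longer take part. Section 2.12 plans an intention-to-treat analysis with multiple imputation for missing data. No section gives an expected rate of loss.

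**The concern.** A 15% figure followed by a larger recruitment target looks like the usual allowance for dropout. Here it is an allowance for ineligibility, and it is spent before anyone is randomised. The 90% power is thus attached to a number randomised that delivers it only if almost every participant has a T2 rating, although the protocol expects that some will not.

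At stake is the accuracy of a headline design property. The comparator is an active, established CBT programme in a superiority design, so if the difference is not significant, readers will ask what the trial was able to detect.

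**Working it through.** **Inputs.** From section 2.7: d = 0.5, power 90%, two-sided alpha 0.05, 86 randomised per arm, 15% unsuitable at baseline, recruitment target of at least 200. From section 2.9: 1:1 allocation. Assumed, because the document gives none: loss by T2 of 5% to 20%, equal in both arms.

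**Step 1: reproduce the stated size.** The normal approximation is n per arm = 2(z₀.₉₇₅ + z₀.₉₀)²/d² = 2(1.960 + 1.282)²/0.25 ≈ 84.1, so 85 per arm. The exact t-test (noncentral t) gives 85.03, so 86 per arm and 172 in total. This is the protocol's figure, reached with no loss at all.

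**Step 2: is there a margin in the rounding?** Exact t-test power is 90.3% with 86 analysed per arm and 89.99% with 85. The margin is about one participant per arm.

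**Step 3: where does the 15% act?** Section 2.7 ties it to the baseline assessment, and section 2.8 randomises only after that assessment. It separates the number assessed (200) from the number randomised (172). It does not separate the number randomised from the number analysed.

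**Step 4: power over an assumed loss range.** Analysed per arm = 86 × (1 − loss); unadjusted complete-case t-test at d = 0.5, two-sided alpha 0.05.

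| Assumed loss by T2 | Analysed per arm | Power |
|---|---|---|
| 0% | 86 | 90.3% |
| 5% | 81.7 | 88.8% |
| 10% | 77.4 | 87.1% |
| 15% | 73.1 | 85.1% |
| 20% | 68.8 | 82.9% |

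At 15% loss (73 per arm), the effect detectable with 90% power is d = 0.54.

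**Side remark on the recruitment target.** 200 × 0.85 = 170, and 172/0.85 = 202.4, so about 203 would have to be assessed for an expected 172 randomised.

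**The case against.** **The planned analysis is not a complete-case t-test.** Section 2.12 specifies a mixed model over three time points with covariates, and multiple imputation. A participant without a T2 rating still contributes baseline data and possibly 12-month data, since section 2.10 continues follow-up after a missed assessment. Under missing at random, that can recover some of the lost information. This stands, and it means the figures above are approximations. It does not remove the point: section 2.7 does not invoke this gain, and no correlation between time points is given from which to size it. Nor can one assume that adjustment for baseline restores 90%, because neither section 2.7 nor section 2.12 specifies a baseline-adjusted T2 contrast as the basis for power.

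**An article may leave such detail to a fuller document.** That would answer a complaint about a missing detail. Here the article states the whole calculation, from effect size to recruitment target, and the 90% claim that follows from it is what needs qualifying.

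**Stronger readings that the document does not support.** A reader might infer that the 90% collapses as soon as anyone misses T2. It does not: the decline is gradual, and power remains about 83% at 20% loss even on the unadjusted approximation. A reader might take 85% as the true power of the trial, but that rests on one assumed loss rate and a simplified test. A reader might also call the target of 200 an error. It is worded as a minimum, so assessing 203 complies with it, and even 170 randomised (85 per arm) gives 89.99% with complete data.

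**Conclusion.** The concern holds in a limited form. The figure of 172 is correctly calculated, but as a number analysed; the protocol uses it as the number randomised and allows nothing for loss between randomisation and T2. The stated 90% therefore requires essentially complete T2 data.

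The effect is modest: a shortfall of about 1 to 7 percentage points over an assumed 5% to 20% loss. This rests on three assumptions: the loss range, which the document does not supply; equal loss in the two arms; and an unadjusted complete-case t-test in place of the planned model, which may lose less. The recruitment arithmetic is a side remark and carries no weight in this conclusion.

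**What to change.** In section 2.7:

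- State that 172 randomised (86 per arm) gives 90% power at d = 0.5 only if T2 data are essentially complete.
- State that the 15% refers to ineligibility before randomisation and is not an allowance for dropout.
- Add power over a range of assumed loss by T2: about 89% at 5%, 87% at 10%, 85% at 15% and 83% at 20%, with d = 0.54 detectable at 90% power at 15% loss. Label these as an unadjusted complete-case t-test approximation at assumed rates.
- Note that the planned mixed model and imputation may recover part of the loss, by an amount that cannot be quantified without a correlation between time points.
- Optionally, mention that about 203 assessed are needed for an expected 172 randomised, which the existing minimum of 200 already permits.

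The cost is a few sentences, with no change to the design, the number randomised or the analysis. The one downside is that the stated power becomes slightly less favourable.
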